### Process evaluation

A key study objective is to understand the process and structures that support the delivery of twice-yearly MDA to guide its scale-up in Ghana and elsewhere in Africa. Therefore, there will be continuous monitoring of all the implementation processes to determine whether the interventions are being implemented appropriately. The monitoring data will also help to determine what needs to change for the intervention to make an impact on the outcome variables to be measured. This would allow for the documentation of all changes that may occur during the implementation process to aid decisions on the scaling up of interventions. The process evaluation will be done using qualitative data collection techniques to generate data to complement the quantitative data to be generated through baseline, midline and end-line surveys as well as provide contextual information to enhance proper interpretations of study results.

Qualitative evaluation will seek to identify and describe key assumptions and conditions underlying the implementation, sustainability and scaling up of the different strategies and delivery systems. The focus of the evaluation will centre on whether CDDs can be utilised for the effective delivery of chemotherapy for control of LF and what factors influence the use of CDDs, including what type of incentives, if any, should be given. Investigation will focus on: (1) community acceptability, which will be assessed using FGDs and in-depth interviews (IDIs) and (2) feasibility, including a situation and stakeholder analysis of the structural, organisational and management factors that enhance or constrain effective implementation [47]. A series of FGDs will be conducted with community members, CDDs and local health officials, to better understand the acceptance and implementation of the interventions, using predefined and structured topic guides. IDIs will be carried out with a range of actors and opinion leaders in order to understand the process and constraints of the different delivery systems. The number of IDIs will depend on when theoretical saturation is reached, but they will include members of the district, regional and national health teams.

FGD participants will be randomly selected from adults aged 18 years and above in each community. It is hoped that a maximum of four FGDs will be conducted in each community, made up of two each of male and female groups. In communities, where there are six or more drug distributers, they will constitute a discussion group; or else in-depth interviews will be conducted with them. Also, FGDs will be conducted with local health officials from the health facility nearest to the study communities. Again, where the numbers are less than six; in-depth interviews will be conducted with them individually.

In-depth interviews will be conducted with two staff each from the district, regional and national health directorates. The selected individuals will be those who are involved in the LF control/elimination programme in one way or another. The place where FGDs and IDIs will be conducted will be left to the convenience of the participants, but with no, or very minimum, interruption during the discussion session. In-depth interviews will also be conducted at a place convenient to the respondent; however, the privacy of the respondent will be ensured.

FGDs and interviews will be digitally recorded, with notes additionally taken, transcribed and translated. Transcripts will be imported into MAXQDA (VERBI GmbH), coded by two independent coders, and analysed using content analysis to identify emerging themes [48]. Following descriptive analysis, patterns and linkages among views, experiences and behaviours of participants will be explored. The collected data will provide important contextual information and a basis for evaluating the generalisability of the study findings.

### Cost analysis

The cost will be estimated as the sum total of expenditures incurred on each treatment arm. An ingredients approach will be used for the collection of cost data, and by consultation of the LF programme accounting system. Standardised frameworks will be used, capturing fixed and recurrent costs incurred at community levels. For the analysis, the cost will include only expenses directly related to the treatment activities. All costs including both cash and in-kind contributions will be used to estimate financial and economic costs of the alternative treatment strategies (annual versus biannual treatment) and delivery systems (through CDDs). Financial costs will reflect the unit cost of the drug distribution and the resources required for its delivery in terms of the actual expenditures incurred. The economic costs will reflect the opportunity cost of all the resources (financial or in-kind contributions) utilised during the intervention. For example, the time spent by health personnel involved in the intervention will represent an economic cost since the personnel are already receiving a salary and may not receive additional income as part of their involvement in the intervention. The financial and economic costs to be assessed will include the direct financial costs, opportunity costs, advocacy, mobilising the community, training of community volunteers and payments made to community volunteers for drug distribution. Other indirect costs, such as expenses made on the surveillance procedures, will not be included in the analysis. It is also important to note that the actual costs of the drugs will not be included in the analysis since these are donated for free to the NTDP. The determination of capital costs will be based on the useful life of equipment including motorbikes, vehicles and other assets. Capital costs will be annuitised using a discount rate of 3% [49]. The costs will also be classified under provider and society-related costs. The provider costs relate to the costs borne by the public health system in providing the intervention, while the societal costs refer to the wider direct and indirect costs not only to the provider but also to the household in terms of their lost time and income. The cost will be analysed in terms of the overall treatment effectiveness, thus providing information on the cost of the intervention strategy and its effectiveness. The cost will also be analysed based on the volume of treatments distributed, thus enabling the determination of cost functions. The treatment interventions will provide protection against LF for a number of months, and the duration of protection offered will have cost implications as it will determine when the next intervention needs to be delivered. Our preliminary data (Table 1) reveal a rise in mf prevalence 6 months after treatment, and thus providing twice-yearly treatment will provide constant protection to the community. To allow greater comparability between the interventions arms the standardised costs of protecting one person for a full year IVM + ALB will be calculated. An important aspect of the cost analysis in terms of programme implementation will be the scale-up of the biannual treatment in other endemic areas with persistent transmission. As such, itemised costing and sensitivity analysis will be undertaken to enable the estimation of the costs of scaled up implementation.

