### Treatment interventions

All study groups will receive treatment with 400 μg/kg IVM + 400 mg ALB, which is highly efficacious against *W. bancrofti* [1]. The difference between the study groups is the frequency of treatment provided (Table 3). The MDA will be implemented in all communities as part of the ongoing NTDP. In Ghana, MDA started in the year 2000 as part of the GPELF. Treatment with 400 μg/kg IVM + 400 mg ALB is provided annually by trained CDDs. Every year, the national team organises training for regional, district, subdistrict supervisors, CDDs and their supervisors. They are also taken through their roles and responsibilities. The programme targets all eligible individuals aged 5 years and above in all endemic districts and communities. The strategies follow the door-to-door Directly Observed Treatment (DOT) strategy [35]. This study will follow the exact MDA strategy used by the NTDP and no modifications other than the frequency of treatment will be made. All treatments will be undertaken through the systems established by the NTDP. Further, the onchocerciasis programme in Ghana undertakes twice-yearly treatment with IVM in hyperendemic areas, and the twice-yearly treatment in LF-endemic areas will be an extension of the onchocerciasis program.

**Table 3 Tab3:** Drug dosage and schedule

Arms	Assigned interventions
Control group	400 μg/kg ivermectin + 400 mg albendazole tablets given every year for 2 years
Expanded frequency group	400 μg/kg ivermectin + 400 mg albendazole tablets given every 6 months for 2 years

Routinely, treatment by the NTDP is done from house to house. CDDs also visit schools to treat after prior notification. Treatment is also done at the markets and sometimes at the church and mosque. Work in the districts is monitored and supervised by coordinators. The team supervisors supervise five or six teams, each of which is made up of two CDDs. Communities are demarcated into sections and marked according to days they are to be visited. Teams under a supervisor work in demarked sections in a ‘sweeping’ fashion one after the other each day (i.e. the whole group move to a section, finish the work there and move to the next). The last day is used to ‘mop up’ though all the sections of the area to which the group has been allocated.

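### The economic cost leaves out donated drugs against the plan's own definition, and the protection premise rests on a microfilaria rise that Table 1 does not show

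*Protocol article*

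**What the plan says.** The Cost analysis section of the protocol article sets a broad scope: "All costs including both cash and in-kind contributions will be used to estimate financial and economic costs of the alternative treatment strategies". It defines the economic part in the same spirit: "The economic costs will reflect the opportunity cost of all the resources (financial or in-kind contributions) utilised during the intervention". Its own example is the time of salaried health staff, which counts as an economic cost although no extra money changes hands. Later in the section, "the actual costs of the drugs will not be included in the analysis since these are donated for free". That exclusion is not limited to the financial cost.

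Table 3 (Treatment interventions) gives the control arm "400 μg/kg ivermectin + 400 mg albendazole tablets given every year for 2 years" and the expanded frequency arm "400 μg/kg ivermectin + 400 mg albendazole tablets given every 6 months for 2 years".

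On duration of protection, the Cost analysis section says that the preliminary data in Table 1 "reveal a rise in mf prevalence 6 months after treatment, and thus providing twice-yearly treatment will provide constant protection to the community". The next sentence announces a standardised cost per person protected for a year as the means of comparing the arms. The section also plans to relate cost to overall treatment effectiveness and to the volume of treatments, and to run a sensitivity analysis for scale-up.

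**The concern.** Two statements in one section do not agree with what they rest on.

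First, a donated tablet is an in-kind contribution. By the section's own definition it belongs in the economic cost, as unpaid staff time does. Leaving it out is not neutral between arms, because one arm uses twice as many rounds.

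Second, the claimed mf rise at 6 months is the stated reason for expecting continuous protection under twice-yearly treatment, and it stands directly before a metric that needs a duration of protection. If Table 1 does not show the rise, that duration has no support.

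Cost-effectiveness is a listed objective (Study aims and objectives), the section treats scale-up as an important use of the costs, and the Discussion expects firm recommendations. Drug supply is also not automatic: Drug manufacturers and supply describes a yearly request sized to the target population and subject to review. The resource implication of doubling the rounds is therefore something a policy reader would want to see.

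**Working it through.** **1. Drug exclusion**

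Inputs: 2 rounds (control) and 4 rounds (expanded frequency) over two years, from Table 3. D = delivery cost per round as the plan would count it; d = value of donated drugs per round; F = yearly cost that does not depend on the number of rounds. The article gives no value for any of the three, so D, d and F are symbols and their ratios below are assumptions.

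- Incremental economic cost over two years, drugs counted: (4 − 2)(D + d) = 2(D + d).
- As planned: (4 − 2)D = 2D.
- Share omitted: 2d / 2(D + d) = d/(D + d).

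| Assumed d/D | Share omitted |
|---|---|
| 0.1 | 0.1/1.1 = 9% |
| 0.5 | 0.5/1.5 = 33% |
| 1 | 1/2 = 50% |

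The effect in the denominator is the same either way, so incremental cost per unit of effect is understated by the same share.

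The ratio of total costs behaves differently. Per year it is (F + 2D + 2d)/(F + D + d).

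- F = 0: the ratio is 2.0 with or without drugs.
- F = D = 1 (illustrative): 3/2 = 1.50 without drugs, and 5/3 = 1.67 with d = 1.

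So omitting drugs lowers the between-arm ratio only when there are fixed costs.

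**2. What Table 1 shows**

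Every printed percentage in Table 1 reproduces from its counts. Exact 95% intervals are added for mf.

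| Time | Antigen (ICT) | mf | mf 95% CI |
|---|---|---|---|
| Before treatment | 48/48 | 17/48 = 35.4% | 22.2–50.5 |
| 3 months | 17/48 = 35.4% | 4/48 = 8.3% | 2.3–20.0 |
| 6 months | 26/48 = 54.2% | 4/48 = 8.3% | 2.3–20.0 |
| 9 months | 23/33 = 69.7% | 3/33 = 9.1% | 1.9–24.3 |
| 12 months | 15/30 = 50.0% | 2/30 = 6.7% | 0.8–22.1 |

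The mf change from 3 to 6 months is zero. Reading the phrase as referring to the time after month 6 does not help: positives go from 4 to 3 to 2 while the denominator falls from 48 to 30, and month 12 is the lowest value. Fisher's exact test gives p = 1.0 for 3 v 6, 6 v 9 and 6 v 12 months (a rough guide only, since the same people are measured repeatedly). The row that rises from 3 to 6 months is antigen, 17/48 to 26/48. The intervals are wide, so a later mf rise is not excluded; it is just not shown. The table follows treated positive individuals, with no twice-yearly dosing and no comparator, so it cannot show protection of a community under that schedule.

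**3. What the duration assumption would do**

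The article gives no formula. As an illustration, credit each round with m months of protection, capped at 12 per year, and count delivery cost only:

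- Annual: D/(m/12). Twice-yearly: 2D/(min(2m, 12)/12).
- m = 6: 2D v 2D, ratio 1.0.
- m = 9: 1.33D v 2D, ratio 1.5.
- m = 12: D v 2D, ratio 2.0.

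The assumed duration alone moves the ratio by a factor of two.

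**The case against.** A reader might infer that the cost analysis makes twice-yearly treatment look cheaper per protected person by construction. The documents do not support that. Without fixed costs, the illustration gives equal cost at 6 months per round and a dearer twice-yearly arm at 12, and adding drugs changes neither ratio. A ratio below 1 needs fixed costs together with a short assumed duration (with F = D = 1 and m = 6, it is 4 v 3, ratio 0.75). The article states neither.

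It would also be wrong to say that the cost results ignore the trial's data. Relating cost to overall treatment effectiveness is already planned, and the cost per protected person is one summary among several. The link from the Table 1 premise to that summary is implied by their adjacency. The reason the section gives for standardising is comparability between arms, and an article may leave the formula to a fuller document.

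The drug exclusion is open and reasoned, and it is coherent for the financial cost. Drugs are not the only resource that doubles: distributor, staff and household time double too, and these are counted. The percentages in the first table depend on assumed prices.

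All of this stands, and it limits the point. It does not remove the two conflicts: the exclusion covers the economic cost as well, and the mf sentence misstates Table 1. The planned sensitivity analysis concerns scale-up and does not name drug value.

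**Conclusion.** The point holds in two limited parts. Excluding donated drugs contradicts the plan's definition of economic cost and understates the incremental economic cost of the twice-yearly arm, and its incremental cost per unit of effect, by d/(D + d): about 9% to 50% for d between 0.1D and D. That range is assumed, and it treats D and d as the same in every round. The between-arm cost ratio is understated only if some costs are fixed.

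The statement about mf at 6 months is wrong against Table 1, and the inference of continuous protection from it is unsupported. Whether this biases the standardised cost depends on a formula that the article does not give. If the premise does set the duration, the comparison can run from parity to a twofold difference on an assumption. Table 1 supports 12 months of protection no better than 6. This matters for the cost-effectiveness objective and should be corrected; it touches neither the randomisation nor the primary outcome.

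**What to change.** - Keep drugs out of the financial cost. Report the economic cost of each arm, and the increment between arms, with and without donated drugs at a stated unit value with its source.
- Correct the mf sentence to match Table 1: mf prevalence was unchanged between 3 and 6 months, and antigen prevalence rose. Drop the inference of continuous protection.
- Make the planned analysis against trial effectiveness the lead cost-effectiveness result, and name its effect measure as the randomised difference in prevalence.
- If the cost per protected person is kept, state its formula. Take duration of protection from data observed in each arm, or vary it in a sensitivity analysis (for example 6, 9 and 12 months per round).

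The cost is one unit price, some rewording and a little extra analysis. The figure for twice-yearly treatment may become less favourable. Trial conduct, sample size and data collection do not change.

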
### Ethics approval and consent to participate

The study (Version 1.2 dated 6 April 2017) was reviewed and approved by the Ethics Committee of the Ghana Health Service (GHS-ERC: 04112/2016). It was also reviewed by the NMIMR IRB (CPN 062/16-17) with Federal Wide Assurance Registration (FWA 00001824). Any substantial changes to the study protocol and other documents will be filed as an amendment with the aforementioned ethics committees. The international standard for the design, conduct, monitoring, and reporting of clinical research of investigational drugs (ICH E6 GCP) will be followed in this study. Compliance with Good Clinical Practice (GCP) standards will enhance the protection of study participants and the integrity of the data collected during the study. In addition, ethical standards and guidelines of Horizon2020 will be adhered to in this study.

Prior to conducting demography and obtaining informed consent, repeated community meetings will be held in all of the villages to communicate the purposes of the study and answer questions at the individual and community level. IVM and ALB, the drugs to be used in this study, are safe and used in the yearly mass treatment for the control of the disease. Even though adverse reactions to the drugs are not common, monitoring of SAEs will be done following the procedures used by the NTDP and all individuals reporting side effects to the drugs will be referred to the nearest hospital and managed appropriately.

All personal information will remain confidential. Laboratory specimens, reports, data collection, and process and administrative forms will be identified by a coded unique identifier to maintain participant confidentiality. Access to collected data will initially be limited to fieldworkers at the point of data collection, and to the study statistician and investigators during analysis. Data to be collected is considered non-sensitive and does not include identifying participant information. Due to the nature of the mandate of the NMIMR, the institute is registered as a data controller with the Ghana National Data Protection Commission and abides by the provision of the Data Protection Act, 2012 (Act 843). Physical data is kept in locked cabinets with access restricted to only the investigators. The IT department provides the facility and secured server where each research fellow can securely store data. Moreover, the IRB requires a yearly report of the study, and may request to evaluate the data at any time. In addition to this, the ethical standards and guidelines of Horizon2020 and the Directive 95/46/EC on Data Protection and Privacy will be rigorously applied, throughout the study. Technical data-protection procedures and privacy/confidentiality measures will be implemented in the project, in compliance with national and European Union (EU) legal framework. Standard operating procedures will be developed to serve as guidelines and training for all study investigators, technicians and field personnel. All individuals who will participate in the proposed research will be required to sign the appropriate SOPs as evidence of training and understanding of the use of participants in biomedical research, and protection of personal data, and the principles for the design, conduct, monitoring, and reporting of clinical research (ICH E6 GCP).

#### Informed consent

This study will be embedded within the activities of the NTDP, which continues to deliver treatment to all endemic communities in the study areas. Written informed consent will be obtained from adults and parents or guardians of children, before enrolment (Additional file 2). Written informed consent will also be sought from individuals included in the qualitative evaluations, including FGDs and in-depth interviews. Participants of FGDs and interviews will be provided the options not to be quoted in any reporting of findings. Written assent to participate in the cross-sectional and longitudinal studies will be obtained from children aged 12 years and above. Risks and benefits of participating in the study will be presented during community meetings and any issues arising discussed. The risk of participating in the trial is very low. The study drugs, IVM and ALB, are safe and severe adverse events are not expected [1, 50]. However, side effects of treatment will be systematically monitored, through the system established by the NTDP. Health-care workers will remain in or near the villages for 48 h after drug administration. People who received treatment will be informed that fever and malaise are potential side effects of the two drugs and antipyretics will be given to those who complain of discomfort. In the unlikely situation of events occurring, these will be reported to the study site investigator and the principal investigator (PI) will inform the Ethics Committees. Collection of blood samples is a routine laboratory procedure. Trained phlebotomists will be used in all blood collection procedures. The potential adverse effects that may result from the study participants are listed below, with information on how to minimise them.

Potential adverse effects, discomfort or risks:Embarrassment in being selected for parasitological surveysDifficulty in collecting bloodLack of adherence with treatmentSide effects from treatment

Steps to be taken to minimise adverse effects, discomfort or risks:The aims and objectives of the study will be explained to the study participants prior to recruitment. Study participants are free to leave the study at any time. All data will be anonymised, and no personal information will be traceable to the consenting participantsOnly trained phlebotomists will be used for blood collection. Best practices for blood collection, including calming the participant, will be employedTreatments will be directly observed by the CDDs, but will not be forced. This will also serve for monitoring compliance to MDA and monitoring side effectsAdverse effects from IVM are minor, including itching, rashes, headache, nausea, vomiting, diarrhea, weakness, drowsiness. All participants will receive information to help identify and promptly report any adverse effects for management. Field personnel will also receive training in monitoring and managing side effects

